### 1.5. Proposed Research Aims and Objectives

The general objective of the research is to determine whether or not GT is an effective treatment for depression in PWD.

Specific objectives of the study are:-To assess if there is a pre/post improvement and, if so, how great this is (clinical significance), according to the outcome variables rates, as well as whether it can be attributed to the therapy intervention.-To assess if study participants suffer with loneliness.-To assess if loneliness is mitigated by the regular contact with the therapist.-To assess if the regular contact with the therapist affects the level of depression.-To assess if a clinical improvement of depression symptoms has an indirect effect on the level of family carers’ burden.-To assess if a clinical improvement has an indirect effect on the mutuality of the relationship between the patient and the family carer.

In order to achieve the objectives, the following research questions will need to be answered:Is there any pre/post treatment improvement?If the answer to question 1 is yes, is the change clinically significant (reduction of symptoms by 50%)?If loneliness is a factor, is the improvement solely due to the social contact with the therapist? ORCan the improvement be attributed to the therapy intervention?Can the improvement of the patient also have an impact on the caregiver’s burden and level of mutuality?

The researchers hypothesised that: depressive symptoms will improve post GT treatment and the improvement will be maintained at follow-up; the level of loneliness, if a factor, can decrease post-treatment and remain so at follow-up; the improvement of symptoms is related to the GT treatment; the level of burden of the family carer will reduce whilst the mutuality in the relationship will increase as the PWD’s depression improves.

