### 2.3. Sample and Recruitment

Recruitment will involve two groups of participants: 6 Gestalt psychotherapists and 12 PWD suffering from depression, with 6 in Italy and 6 in Mexico, respectively. The sample size has been chosen on the basis of recommendations provided for SCED in GT, which state that a number of 4 to 10 cases can give the study an international validation for the efficacy of the method for a specific type of problem [70]. For this research, the study number is slightly higher to include a dropout rate of 20–30%. In line with the above, the researchers decided to have as an inclusive approach as possible, with the twofold aim of giving a chance of treatment to patients with different types of dementia (i.e., for compassionate reasons) and observing its impact on them (i.e., for research interest).

To be part of the study, PWD will need to: (a) provide evidence of a formal diagnosis by a medical doctor, i.e., a neurologist, geriatrist, or psychiatrist; (b) have a clinical dementia rating–sum of the boxes (CDR-SOB) score of 3–4 (very mild dementia) or 4.5–9 (mild dementia) [71]; (c) be able to engage in therapy; (d) display symptoms of mild depression, i.e., geriatric depression scale (GDS) score 10–19 [72] and/or anxiety (neuropsychiatric inventory anxiety subscale, NPI-A score ≥ 4 [73]); (e) maintain the psychopharmacological treatment during the investigation; f) live in the community.

Exclusion criteria are: (a) diagnosis/symptoms of dementia at a moderate–severe stage (given by a medical specialist) or CDR-SOB score of 9.5–18; (b) display of challenging behaviours, delusions, or psychotic symptoms or major depression (GDS score between 20–30); (c) high level of risk and safeguarding issues; (d) parallel therapy/intervention for the same target complaint (e.g., psychoeducational groups); (e) variation in psychopharmacological treatment during the investigation; (f) admission to hospital/residential care.

Gestalt psychotherapists included will need to: (a) agree to participate, be recorded during sessions, and fill in questionnaires; (b) be state licensed Gestalt psychotherapists, with previous experience of working with PWD; (c) have access to supervision with a Gestalt supervisor.

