### 2.4. Measures and Data Collection Tools

Overall, data will be collected through questionnaires and audio/video recording. Outcome measures will gather quantitative data on the symptoms, quality of life, level of loneliness, family carers’ burden, and mutuality and will be administered at session “0”, at the final session and follow-up (week 2 and week 24), whilst target complaints will be repeated daily and used for the time series analysis. All the measures and related administration time points are shown in Table 1 and described below.

The Neuropsychiatric Inventory Questionnaire (NPI) was developed by Cummings et al. [73] and validated by Binetti et al. [74] for the Italian population and by Zepeda et al. [75] for the Mexican population. It measures the behavioural symptoms related to dementia conditions, assessing twelve sub-domains: delusions, hallucinations, agitation/aggression, depression/dysphoria, anxiety, elation/euphoria, apathy/indifference, disinhibition, irritability/lability, motor disturbance, night-time behaviours, and appetite/eating. Additionally, a caregiver distress scale was included for measuring the psychological impact of the neuropsychiatric symptoms on family caregivers [76]. The NPI anxiety (NPI-A) score will be used to assess the level of anxiety of participants at pre/post treatment. The test has good internal consistency, content validity, and inter-rater/test-retest reliability.

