### 2.5. Data Analysis

Continuous variables will be analysed and reported as mean ± SD (standard deviation) or median and IQR (interquartile range), on the basis of their distribution (assessed through Shapiro–Wilk test). Discrete variables will be reported as absolute frequencies and percentage.

In order to evaluate any pre/post improvements (from baseline to follow-up: at the final session, after two weeks and twenty-four weeks following the end of the treatment) in the main outcomes, i.e., depression and anxiety symptoms (GDS; NPI-A), quality of life (QOL-AD), and the therapy outcome (CORE–OM), three types of analysis will be carried out: (a) visual analysis, comparing the target complaint (TC) scores during the three phases; (b) mean difference from baseline to follow-up tested, by means of paired t-test or Mann–Whitney U test, according to the distribution of the outcome variable [99]; (c) mean baseline reduction (MBLR) for obtaining the effect size for single-case designs [100,101,102], as follows:MBLR = (Mean of Baseline phase − Mean of Follow-up phase) × 100/Mean of Baseline phase.(1)

The same procedure will be applied for the secondary outcome, i.e., loneliness. Additionally, data collected from family caregivers (i.e., QOL-AD family version, caregiver burden scale, and the mutuality scale) during the three phases of the study will be compared with subjects’ outcomes, in order to evaluate indirect effects of the treatment, by means of Pearson or Spearman correlation coefficients, as appropriate.

Blind raters will assess the fidelity of the approach by rating a small sample of sessions through the GTFS.

A two-tailed *p* value < 0.05 will be considered significant. Data will be analysed using SPSS for Windows V24.0 (SPSS Inc., Chicago, IL, USA) and Simulation Modeling Analysis (SMA) for Windows V07.30.20 (ClinicalResearcher, Jeff Borckardt, Medical University of South Carolina).

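### The non-normal alternative to the paired t-test is the Mann–Whitney U test, which ignores the pairing and, for positively correlated scores, is over-conservative

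*Protocol article*

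**What the plan says.** Section 2.5 lists three analyses of pre/post improvement in depression, anxiety, quality of life and therapy outcome (GDS, NPI-A, QOL-AD, CORE–OM). Item (a) is visual, item (c) is a percentage reduction, and item (b) is the hypothesis test: "mean difference from baseline to follow-up tested, by means of paired t-test or Mann–Whitney U test, according to the distribution of the outcome variable". The same procedure is applied to loneliness. The significance rule is "A two-tailed *p* value < 0.05 will be considered significant".

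The section's only stated method for judging distribution is in its opening sentence on describing continuous variables: "on the basis of their distribution (assessed through Shapiro–Wilk test".

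Section 2.4 says that the outcome measures "will be administered at session “0”, at the final session and follow-up (week 2 and week 24", so each participant supplies both the baseline and the later scores. Section 2.3 recruits "6 Gestalt psychotherapists and 12 PWD suffering from depression, with 6 in Italy and 6 in Mexico, respectively". There is one treated group and no control arm.

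**The concern.** The first option in item (b) treats the data as paired. The second treats the same data as two independent samples. Non-normality is a reason to move to ranks, but it does not remove the link between a person's first and second score. The non-parametric counterpart of the paired t-test is a paired rank test, and section 2.5 names none.

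The trigger is also loosely placed. It refers to the distribution of the outcome variable, whereas the paired t-test depends on the distribution of the within-person differences. Skewed raw scores can have fairly symmetric differences, so the unsuitable branch may be entered when the t-test would have been acceptable.

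What is at stake is the p-value for the first research question, whether there is any pre/post improvement. Of the three listed analyses, only item (b) is described as a significance test.

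**Working it through.** **Sample size.** The article gives no power calculation to reproduce. Its 12 participants come from a recommendation that "a number of 4 to 10 cases can give the study an international validation", after which "the study number is slightly higher to include a dropout rate of 20–30" per cent. Taking the upper figure of 10 cases and 20% dropout, 10 × 1.20 = 12, which matches. Expected completers are 12 × 0.80 = 9.6 and 12 × 0.70 = 8.4.

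**Direction of the error.** Let scores have SD σ at both times and within-person correlation ρ. The variance of the difference in means is 2σ²(1 − ρ)/n if pairing is respected and 2σ²/n if it is ignored. The ratio is 1 − ρ: 0.50 at ρ = 0.5 and 0.24 at ρ = 0.76. Ignoring pairing therefore raises the effective critical value from 1.96 to about 1.96/√0.50 = 2.77 or 1.96/√0.24 = 4.00. Rank tests behave similarly. Simulated type I error at n = 12 with normal scores and nominal two-sided 5%:

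| Correlation | Mann–Whitney | Signed-rank |
|---|---|---|
| 0.5 | 0.8% | 4.2% |
| 0.7 | 0.2% | 4.5% |
| 0.76 | 0.1% | 4.4% |

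**Inputs for power.** The article gives no SD, skew or correlation for these scales, so all of these are assumed. The value 0.76 is the test-retest figure that section 2.4 quotes for target complaints. It is a stand-in from a different instrument, and 0.5 is a lower alternative. The plan's whole rule is modelled as Mann–Whitney if Shapiro–Wilk gives p < 0.05 at either time point, and paired t otherwise. That reading is also an assumption.

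**Power at n = 12, 0.6 SD shift.**

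| Scores | Correlation | Fallback used | Mann–Whitney alone | Plan's whole rule | Signed-rank |
|---|---|---|---|---|---|
| Normal | 0.76 | 8–11% | 17% | 75% | 74% |
| Normal | 0.5 | 8–11% | 21% | 46% | 42–44% |
| Log-normal, sigma 0.5 | 0.76 | 45–52% | 34% | 61% | 78% |
| Log-normal, sigma 0.5 | 0.5 | 45–52% | 37% | 48% | 52% |
| Log-normal, sigma 1 | 0.76 | 86–92% | 84% | not tabulated | 88% |
| Log-normal, sigma 1 | 0.5 | 86–92% | 81% | not tabulated | 74% |

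The cells come from separate simulation runs, some with 800 replicates, so the Monte Carlo standard error can reach √(0.5 × 0.5/800) = 1.8 points.

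**Fewer completers.** With skewed (log-normal) scores, n = 9 and correlation 0.7, Mann–Whitney against signed-rank is 17% against 49% for a 0.5 SD shift and 52% against 77% for 0.8 SD. These figures assume that the fallback has been used.

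**GDS-like scores.** Baseline scores were drawn from the entry range 10–19, with n = 9 and again assuming that the fallback is used. A mean reduction of 15% gives 16% against 71%. A mean reduction of 25% gives 55% against 88%. At 50%, the size named in section 1.5 ("is the change clinically significant (reduction of symptoms by 50" per cent), both are near 100%. If participants admitted for anxiety alone widen the range to 3–19 (assumed), the 50% case becomes 81% against 100%.

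**The trigger.** In a skewed log-normal setting at n = 9, Shapiro–Wilk rejected at least one set of raw scores in about 55–58% of runs, but the differences in only about 20–24%.

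**The case against.** The case for treating this as minor is substantial.

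First, comparing Mann–Whitney with signed-rank on normal scores (17% against 74%) might lead a reader to infer that most of the power is lost and that real improvement will probably be missed. That comparison describes a branch the plan seldom enters with such scores. There the paired t-test is usually run, and the whole rule does about as well as signed-rank throughout. This part of the objection stands.

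Second, where the fallback is used most, with strong skew, Mann–Whitney can match or beat signed-rank. It also has near-full power for a 50% reduction from GDS 10–19. This stands too.

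Third, at positive correlation the error is conservative. A reader might infer that the wrong test could produce a false claim of efficacy in this uncontrolled study, but the calculations show the reverse.

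Fourth, item (b) is not the only evidence. Visual analysis and percentage reduction accompany it, and daily target complaints are intended for time series analysis.

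Fifth, the Shapiro–Wilk sentence concerns descriptive reporting, and the reference to the outcome variable may be condensed wording that covers the change score. The trigger point is therefore a clarification and not a proven error.

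None of this makes an independent-samples test suitable for repeated measurements on the same people. A within-case reading does not help, because each participant has a single baseline value on these scales. Nor is this a detail left to an unseen analysis plan: the article names the test.

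**Conclusion.** The plan is wrong as written and should be fixed. When the fallback is used, pairing is ignored and the p-value is miscalibrated. For positively correlated scores it is too large on average, with an actual type I error of about 0–1% at n = 12.

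The practical loss is conditional. It is material when scores are moderately skewed and clearly correlated: at sigma 0.5 and a 0.6 SD shift, the whole rule loses 78 − 61 = 17 points at correlation 0.76 and 52 − 48 = 4 points at 0.5. It is small or absent with near-normal scores, strong skew, correlation near zero or very large effects. The article gives no distribution, SD or correlation for these scales, so it supports neither a general statement that improvement will be missed nor one that the fallback will often be used.

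These conclusions rest on the assumed correlations, the log-normal form and the assumed reading of the switching rule. If the within-person correlation were negative, the variance ratio shows that the error would run the other way.

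**What to change.** In item (b) of section 2.5, replace the Mann–Whitney U test with the Wilcoxon signed-rank test on the within-person differences, and state that the choice between it and the paired t-test rests on the distribution of those differences. Carry the same wording over to loneliness. Using the signed-rank test throughout would remove the switch altogether, but that is optional.

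The cost is one sentence. Design, sample size and data collection are unchanged.

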## 2. Materials and Methods

### 2.1. Research Design

The ABA single-case experimental design will be used for the purpose of the study, as explained previously.

The research method is divided into three phases: an “A” baseline period of two weeks between the assessment session “0” and initial psychotherapy session; a “B” intervention period of minimum eight GT sessions; an “A” follow-up period of six months after the end of the intervention, with measurements at the final session, after two weeks and six months. More specifically, in relation to data collection, the following will happen in each phase: A—at the baseline, outcome measures will be administered at session “0”, and individual target complaints (TC) will be recorded daily for the following two weeks; B—in the intervention phase, target complaints will be completed daily; A—in the follow-up phase, participants will continue with daily assessment for another two weeks, while outcome measures will be administered at the final session, i.e., week two and week twenty-four (Figure 1).

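### The rank alternative to the paired t-test is Mann–Whitney U, an independent-groups test, although every pre/post comparison is within the same patients

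*Protocol article*

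**What the plan says.** Section 2.5 (Data Analysis), item (b), gives the inferential test for change: "mean difference from baseline to follow-up tested, by means of paired t-test or Mann–Whitney U test", with the choice between the two depending on how the outcome is distributed. The outcomes it covers are "depression and anxiety symptoms (GDS; NPI-A), quality of life (QOL-AD), and the therapy outcome (CORE–OM"). Loneliness is added in the next paragraph: "The same procedure will be applied for the secondary outcome, i.e., loneliness". Significance is two-tailed at 0.05, and distribution is assessed with the Shapiro–Wilk test.

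The data come from repeated measurement of the same people. Section 2.4 says the outcome measures "will be administered at session “0”, at the final session and follow-up (week 2 and week 24"), and Table 1 lists the same occasions scale by scale. Section 2.1 sets the design: "The ABA single-case experimental design will be used for the purpose of the study". Section 2.3 plans "12 PWD suffering from depression, with 6 in Italy and 6 in Mexico, respectively". There is no untreated or comparison group, and item (b) makes no comparison between countries.

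**The concern.** Item (b) offers two tests for one question and they assume different data structures. The paired t-test works on each participant's own change. Mann–Whitney U compares two independent samples and makes no use of which follow-up score belongs to which baseline score. With one group measured repeatedly, its independence assumption fails by design. No paired rank test is named anywhere in the article.

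This does not depend on how the choice between the tests is triggered. Whatever sends an outcome to the rank test, the test it reaches does not fit the data. It is also not a detail left to a fuller document, because the article names a specific test.

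At stake is the first research question in section 1.5, whether there is any improvement from before to after treatment. Depression, the primary variable according to section 2.4, is among the outcomes tested this way. An outcome sent to the fallback would normally face a much stricter hurdle than one that stays with the paired t-test, for a reason unrelated to treatment.

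**Working it through.** The article states no power, SD or effect size for this test, so there is no figure of its own to reproduce.

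**Inputs from the protocol article**
- Participants: 12 (section 2.3). Dropout is 20–30%, so 12 × 0.8 = 9.6 and 12 × 0.7 = 8.4, or about 8 to 10 completers.
- Two-tailed alpha 0.05 (section 2.5).
- GDS entry range for mild depression 10–19 (section 2.3), used only to set the scale.

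**Assumptions not in the documents**
- Integer scores with mean 14 and SD 3, and a true fall of 2 points.
- Pre/post correlation ρ of 0.5 to 0.7, with other values shown as a range.

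**Step 1: why the error rate moves.** For a mean change, the variance if the two occasions were independent is 2σ²/n. For the same people it is 2σ²(1 − ρ)/n. A test that assumes independence therefore uses an effective critical value of about 1.96/√(1 − ρ). The large-sample type I error that follows is set beside the simulated Mann–Whitney error (n = 12, normal scores, 10,000 runs):

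| ρ | 1.96/√(1 − ρ) | Approximate error | Simulated error |
|---|---|---|---|
| −0.3 | 1.72 | 8.6% | 7.5% |
| 0 | 1.96 | 5.0% | 4.6% |
| 0.3 | 2.34 | 1.9% | 2.1% |
| 0.5 | 2.77 | 0.6% | 1.0% |
| 0.7 | 3.58 | 0.03% | 0.2% |

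The signed-rank test stayed between 3.7% and 4.7% in the same simulations.

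**Step 2: power once the fallback is used** (integer scores, SD 3, 2-point fall):

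| n | ρ | Mann–Whitney | Signed-rank |
|---|---|---|---|
| 12 | 0.5 | 28% | 54% |
| 12 | 0.7 | 24% | 74% |
| 9 | 0.5 | 17% | 40% |
| 9 | 0.7 | 15% | 59% |

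For a larger change of 0.8 SD on normal scores at n = 12, the figures are 42% against 66% at ρ = 0.5 and 42% against 87% at ρ = 0.7.

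**Step 3: a worked example.** Twelve baseline GDS scores within the entry range: 10, 11, 12, 13, 14, 15, 16, 17, 18, 19, 12, 16. Falls: 2, 3, 1, 2, 3, 2, 1, 3, 2, 2, 3, 1. Every patient improves, and the mean fall is 25/12 = 2.1.
- Mann–Whitney: U = 99, against 12 × 12/2 = 72 expected under no difference. Without the tie correction the SD is √(12 × 12 × 25/12) = 17.3, so z = (99 − 72 − 0.5)/17.3 = 1.53. With the tie correction, p = 0.12.
- Exact signed-rank: all 12 differences have the same sign, so p = 2/2¹² = 0.0005.

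This example is deliberately clear-cut, since its pre/post correlation is about 0.97.

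**The case against.** The choice of test is not seriously defensible. The objections concern how much harm it does.

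- **The fallback is conditional.** If distribution does not call for it, the valid paired t-test is used. With near-normal simulated scores and Shapiro–Wilk applied to the two sets of scores (one reading of the rule), the fallback was triggered in about 14% of runs. Power of the whole rule at n = 12 was then 51% against 55% for always using the paired t-test at ρ = 0.5, and 69% against 74% at ρ = 0.7. This stands: averaged over such data the loss is a few percentage points, and the large gap applies to an outcome that reaches the fallback. A scale with a skewed distribution would reach it more often.
- **The direction depends on the correlation.** This also stands. At zero correlation the two tests perform about alike, and at a negative correlation Mann–Whitney is too liberal (7.5% at −0.3). For a pure shift in strongly skewed (log-normal) scores at n = 12, Mann–Whitney was not less powerful until ρ reached about 0.7, although its error at 0.7 was still 0.2%.
- **The test is one of three analyses.** Visual analysis of the target complaints and the mean baseline reduction are unaffected, and under positive correlation the error does not create false claims of benefit. That is true, but item (b) is the only one of the three that gives a significance test of change.
- **The test might be meant for the daily target complaints, phase against phase.** The text does not support this: item (a) gives the target complaints to visual analysis, and item (b) puts the test beside a paired t-test.

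**Conclusion.** The concern holds. Mann–Whitney U is wrong as written for a comparison of the same participants before and after treatment, and it contradicts the paired t-test named next to it. That conclusion follows from the design and needs no assumption.

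The size does rest on assumptions. For an outcome that reaches the fallback, with SD 3, a 2-point fall and a correlation of 0.5 to 0.7, power at 12 patients is about half to one third of what a paired rank test gives, and the real type I error is about 0.2–1%, not 5%. Positive correlation between repeated scores in one person is usual, but the article gives no value. The test is therefore more likely to miss a real improvement; it will not always do so.

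**What to change.** In section 2.5, item (b), replace the Mann–Whitney U test with the Wilcoxon signed-rank test on within-participant differences, for the main outcomes and for loneliness. An exact sign-flip permutation test of the mean difference would also serve. Two small additions would help: assess normality on the paired differences, and report the median paired difference with its confidence interval.

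Exact p-values are advisable at this sample size, and the test remains usable after dropout. With 8 completers who all improve, the smallest two-sided p is 2/2⁸ = 0.008.

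The cost is one phrase. The test is a standard procedure, and no visit, measurement or participant is added.

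### The only single-case effect size compares baseline with follow-up, so for the daily target complaints it cannot separate a response during therapy from a change that appears after therapy ends

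*Protocol article*

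**What the plan says.** Section 2.1 of the protocol article sets the design: "The ABA single-case experimental design will be used for the purpose of the study". In the first A phase "individual target complaints (TC) will be recorded daily for the following two weeks". During therapy the same ratings continue: "B—in the intervention phase, target complaints will be completed daily". They then run for two more weeks after therapy. The questionnaires are given only at session 0, the final session, week 2 and week 24 (sections 2.1 and 2.4, Table 1). Section 2.4 assigns the target complaints to the time series analysis.

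Section 2.5 lists three analyses of improvement from baseline to follow-up:

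- (a) "visual analysis, comparing the target complaint (TC) scores during the three phases";
- (b) a test of the mean difference from baseline to follow-up;
- (c) "mean baseline reduction (MBLR) for obtaining the effect size for single-case designs", with the numerator and denominator printed as "Mean of Baseline phase − Mean of Follow-up phase) × 100/Mean of Baseline phase".

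The SMA program is named as software, but the article does not say which phases it will compare. Section 1.5 asks whether there is improvement, whether it reaches a 50% reduction, and whether it can be attributed to the therapy. It also hypothesises that "depressive symptoms will improve post GT treatment and the improvement will be maintained at follow-up".

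**The concern.** In a single case, the most direct evidence that therapy did something is a shift in the score when therapy begins. Formula (1) has no term for the intervention phase. The target complaints are the only outcome that could show such a shift, because they alone are rated repeatedly in all three phases. If the formula is used on them, the effect size describes the state in the two weeks after therapy has stopped, relative to the state before it started.

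Two separate claims then share one number: that symptoms improve with treatment, and that the gain is kept. A reader of the results could not tell from the effect size which of the two was observed. The intervention-phase ratings would be read only by eye, with no magnitude to set beside the 50% criterion.

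**Working it through.** **No stated figure to reproduce.** The article gives no numerical effect size, so the check applies formula (1) to illustrative series.

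**Inputs from the article.** Baseline is two weeks of daily ratings, 14 days. The intervention is at least eight weekly sessions, taken as 8 × 7 = 56 days. Follow-up ratings run for two weeks, 14 days. The scale is 1 to 10, higher meaning worse. The clinical-significance criterion is a 50% reduction.

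**Assumed inputs.** The phase means below are illustrations within the 1 to 10 scale. None comes from the article.

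**Share of ratings not entering the effect size.** 56 / (14 + 56 + 14) = 56/84 = 67%. Counting the intervention as about 50 days, from the first to the eighth session, gives 50/78 = 64%.

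**Formulas.** Write A1, B and A2 for the means of the baseline, intervention and follow-up phases.

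- As printed: (A1 − A2) × 100 / A1.
- Same index, baseline against intervention: (A1 − B) × 100 / A1.

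| Pattern (A1/B/A2) | As printed | Baseline against intervention |
|---|---|---|
| Maintained response, 8/4/4 | (8 − 4) × 100/8 = 50% | (8 − 4) × 100/8 = 50% |
| Flat in therapy, falls afterwards, 8/8/4 | (8 − 4) × 100/8 = 50% | (8 − 8) × 100/8 = 0% |
| Response that reverses, 8/2/8 | (8 − 8) × 100/8 = 0% | (8 − 2) × 100/8 = 75% |
| No change, 8/8/8 | 0% | 0% |

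The printed formula gives the first two patterns the same value, exactly at the 50% criterion. It also gives the third and fourth the same value, 0%.

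**Sensitivity to where the final-session day falls.** If that day is counted as follow-up, 8/2/8 has a follow-up mean of (2 + 14 × 8)/15 = 7.6 and gives 5%. For 8/8/4 the mean is (8 + 14 × 4)/15 = 4.27, which gives 46.7%. The conclusion does not change.

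**What the alternative contrast does not solve.** Take a straight-line drift from 8 on day 1 to 3 on day 84 with no therapy effect. The daily step is 5/83 = 0.0602. The means are:

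- baseline: 7.61;
- whole intervention phase: 5.50;
- last 14 intervention days: 4.24;
- follow-up: 3.39.

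The printed formula gives (7.61 − 3.39)/7.61 = 55%. Baseline against the whole intervention phase gives (7.61 − 5.50)/7.61 = 28%. Baseline against the last 14 intervention days gives (7.61 − 4.24)/7.61 = 44%. A baseline-against-intervention value is less affected by this drift, but not free of it.

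**The case against.** The strongest reply is that the article never says the formula is applied to the target complaints. The sentence that introduces the three analyses names depression, anxiety, quality of life and CORE–OM, and the target complaints appear by name only under the visual analysis. This stands as a caveat. On the other side, the questionnaires have a single baseline value per participant, so a per-participant mean of a baseline phase can be formed only from the daily ratings. A mean across participants is possible, and the article uses the word phase loosely: it speaks of carer data in three phases although the carer scales are taken only at session 0, the final session and follow-up. The point is therefore conditional on the formula being used for the target complaints.

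Second, baseline to follow-up suits the hypothesis of a maintained gain. Under that hypothesis, 0% for a response that has reversed is a correct answer about maintenance. That also stands, and it is a reason to keep the formula under a clear label. It does not supply the size of the response during therapy.

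Third, the visual analysis covers all three phases and could expose either problem pattern, and the SMA program may be intended for a phase comparison that the full protocol describes. Both are fair, and the lack of SMA detail in an article is no fault in itself. What the article does fix is the effect size, and that has no intervention term.

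A reader might infer that the plan credits Gestalt therapy with change that occurs after it ends. The article does not say so. It treats attribution as a separate question and does not state that this index answers it.

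**Conclusion.** The point holds in a limited form. As printed, the only named single-case effect size cannot distinguish a maintained on-therapy response from a change that first appears after therapy, and it gives 0% to a response that reverses. This follows from the formula whatever the score levels; the levels in the table are illustrations. It matters only if the formula is applied to the target complaints, which is the natural reading but not an explicit one. In that case about two thirds of the daily ratings at minimum therapy length inform only the visual analysis.

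Two wider readings are not supported. The intervention phase is not ignored by the plan as a whole, because the visual analysis includes it. Nor is the formula wrong for GDS, NPI-A, QOL-AD, CORE–OM or loneliness: these have no measurement inside the intervention phase before the final session, so its absence follows from the schedule.

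No probability of meeting the 50% criterion is given here, because the article states no variability or autocorrelation for the target complaints. The change is a worthwhile, inexpensive improvement to how attribution is assessed. It does not settle attribution by itself.

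**What to change.** In section 2.5, state that two values are reported per participant for the target complaints:

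1. **On-treatment effect:** (baseline mean − intervention mean) × 100 / baseline mean. Say in advance whether the intervention mean covers the whole phase or a fixed window at its end. Accompany it with the autocorrelation-adjusted baseline-versus-intervention comparison in the SMA program already named.
2. **Maintenance:** the present formula, baseline against follow-up, labelled as such.

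Add that attribution is interpreted from the first value together with the visual analysis and any trend visible in the baseline, since the first value alone does not remove a time trend. Leave the questionnaire analyses unchanged in this respect.

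The daily ratings and the software are already planned, so no visits, participants or instruments are added. The cost is one further calculation, and two effect sizes to report per participant instead of one.
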